**Methods and analysis:**

Individuals (~1000) living in the same household as a case diagnosed with pulmonary TB (n = 250) or in a neighbouring household (~4500 individuals) will be screened for TB symptoms and by chest x-ray. Two sputum samples will be collected for microbiological analysis from anyone with a productive cough. Any person found to have TB will be treated by the National TB Control Program. All those with no evidence of TB disease will have a repeat screen at 12 months. Whole-genome sequencing (WGS) and social network analysis (SNA) will be conducted on Index cases and contacts diagnosed with TB.

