*Data collection and screening algorithm*. For each Index case, socio-demographic information and results from their Acid-fast bacilli (AFB) smear and/or Xpert MTB/RIF testing at the CHC or hospital will be obtained. Sputum samples will be sent to the research laboratory for culture and storage. From each consenting household contact a symptom screen will be undertaken (Fig 2) as well as enquiry about any history of TB, whether they are on any TB preventive therapy, have any other immunocompromised medical condition, and their socio-demographic information (age, gender, ethnicity, smoking status). The location of each household will be recorded using an electronic geographic coordinate system. Any person with symptoms suggestive of TB (weight loss, night sweats, fever, chest discomfort or pain) will undergo clinical assessment. Any person with a productive cough of any duration will be asked to provide two sputum samples for AFB smear and/or Xpert MTB/RIF testing, and *Mtb* culture [17, 18]. All participants will be offered a chest x-ray, followed by sputum examination if the x-ray has changes suggestive of TB. Chest x-ray reports will be read by a radiologist. Cases with a radiology report showing indication of TB without bacteriology positivity will be consulted to an infectious disease specialist to determine whether they should receive TB treatment or not. All diagnostic procedures and treatment for any person found to have TB will be undertaken according to National TB guidelines.

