#### 2) Whole-genome sequencing and social network analysis

From each household contact who is diagnosed with TB, as well as Index cases, an interview will be undertaken using a social network questionnaire, and sputum cultured for Mtb will undergo WGS to ‘fine map’ their relatedness [19]. We will use the BWA-MEM algorithm to map the sequence data to the H37Rv reference genome. Variants will be called using Pilon (v1.22). We will assign a call as missing if the valid depth at a specific site is less than 12, if the mean read mapping quality at the site does not reach seven, or if none of the alternative alleles account for at least 85% of the valid coverage.

Pairwise genetic distances between each TB patient will be determined, after removing single-nucleotide polymorphisms (SNPs) in highly repetitive genes such as the PE/PPE genes and loci under strong selection. [20, 21]. For all pairs, we will obtain the shortest travel time between two points as an approximation of the geographic distance using Open Source Routing Machine, a publicly available tool that analyses Open Street Map road network data. We will assess the relationship between geographic and genetic distance across all pairwise samples to determine the relative contribution of close versus distant contacts in TB transmission. For five definitions of SNPs distances (0–1, 2–3, 4–5, 6–10, and 11–30 SNPs different), we will first compare the odds of genetic relatedness at each of the five levels among pairs within the household, pairs within the neighbourhood, and pairs from different neighbourhoods. We will repeat the same but classifying the pairs in to five categories (within the household, 0–5, 5–10, 10–20, and 20 or more minutes of travel time apart). We will also determine whether any of the household contacts share common meeting places such as employment venues, places of worship, markets, or restaurants.

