## Discussion

The World Health Organization (WHO) 2020 Global TB Report showed Indonesia had the second highest TB incidence in absolute numbers [1]. In 2015, the National TB Program budget was estimated to be 133 million US dollars, much of which is unfunded [15]. This study will confirm whether neighbourhoods in the vicinity of routinely diagnosed TB index cases constitute a high-risk sub-population that may warrant active intervention to enhance TB control. Evidence provided will be crucial for the Indonesian TB Control Program in scaling up efforts towards the elimination of TB in a targeted and cost-effective way.

The combination of high precision genotyping, expanded social network questionnaires, and network analyses provides the opportunity to explore *Mtb* transmission. Genomic and social network analyses will provide important information to guide the design of possible interventions that may include active case finding, preventive treatment, and/or enhanced infection control measures in specific locations. For example, if ‘recent’ transmission of *Mtb* from index case households to neighbourhoods is indicated as explaining a large component of high neighbourhood prevalence, an intensive intervention of active case finding for early diagnosis and treatment would be warranted. If transmission ‘hotspots’ within the neighbourhoods can be identified, infection control measures could be considered. If high prevalence and incidence of TB is confirmed but there is a relatively low rate of genomic match within neighbourhoods, it may be that socioeconomic factors that promote reactivation are predominant. An intervention of screening for latent TB infection and initiation of preventive treatment to reduce the possibility of reactivation could be considered, or the focus could be on socioeconomic factors themselves, as suggested by WHO as part of the global strategy to End TB [23].

The proportion of TB cases that can be included in the analysis will be crucial to the ability to interpret these data. As COVID-19 continues to be prevalent in Indonesia, it is possible that recruitment and follow-up will be hindered with fewer than expected numbers being included in the study. This information will be closely monitored and every attempt made to follow-up participants through regular phone contact.

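### Shared meeting places among TB cases are not related to genetic distance, so sharing alone cannot support the hotspot inference considered in the Discussion

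*Protocol article*

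**What the plan says.** In the Protocol article, section *2) Whole-genome sequencing and social network analysis*, the questionnaire is limited to people with disease: "From each household contact who is diagnosed with TB, as well as Index cases, an interview will be undertaken using a social network questionnaire". The abstract agrees: "Whole-genome sequencing (WGS) and social network analysis (SNA) will be conducted on Index cases and contacts diagnosed with TB". The baseline items listed for screened participants under *1) Prospective cohort study* include no meeting places.

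The only stated use of the venue data is: "We will also determine whether any of the household contacts share common meeting places such as employment venues, places of worship, markets, or restaurants".

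The same section gives geography a proper comparison. It plans that "Pairwise genetic distances between each TB patient will be determined", and for five bands of SNP distance "we will first compare the odds of genetic relatedness at each of the five levels among pairs within the household". The other two groups compared are neighbours of the same Index case and cases drawn from separate neighbourhoods. The section then repeats this by travel-time category. Venues have no counterpart.

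The Discussion says: "If transmission ‘hotspots’ within the neighbourhoods can be identified, infection control measures could be considered". It also says, in general terms: "The combination of high precision genotyping, expanded social network questionnaires, and network analyses provides the opportunity to explore" transmission. It gives no method for venues.

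**The concern.** Whether cases share a venue is uninformative about transmission unless one knows how often they would share it without transmission. People in an Index household and the five nearest houses may well use the same market or place of worship simply because of where they live. Only cases are asked, so the people screened without TB cannot supply the background frequency. The stated analysis does not use the other available reference either, namely case pairs whose isolates are not closely related.

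At stake is the secondary, location-specific inference. A shared-or-not result will tend to pick out popular places, and the Discussion considers infection control measures where hotspots are identified. The prevalence and incidence outcomes do not depend on this.

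**Working it through.** **1. The plan's nearest figure.** No figure is stated for venues. The closest is the power for household versus neighbourhood genomic identity in *Sample size*: 60% of 35 against 30% of 75, at the 0.05 level (two-sided assumed), stated as over 80%.

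- Pooled proportion = (21 + 22.5)/110 = 0.395.
- Null SE = √[0.395 × 0.605 × (1/35 + 1/75)] = 0.100.
- Alternative SE = √[0.24/35 + 0.21/75] = 0.098.
- z = (0.30 − 1.96 × 0.100)/0.098 = 1.06, so power is 85.5%.

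The stated figure reproduces. The same counts and formula are used in step 4.

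**2. Sharing between two unrelated people.** The documents give no venue-use rates, so p (probability of using a given venue) and k (number of venues) are assumptions, with independent use. P(share at least one) = 1 − (1 − p²)^k.

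| p | k = 3 | k = 5 |
|---|---|---|
| 2% | 0.1% | 0.2% |
| 10% | 3.0% | 4.9% |
| 20% | 11.5% | 18.5% |
| 30% | 24.6% | 37.6% |
| 50% | 57.8% | 76.3% |

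For low use, sharing is rare in any one pair. For the main local market or place of worship it could be common.

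**3. Sharing somewhere among the cases.** This is a different quantity: the chance that at least two of n cases use one given venue, if a fraction q (assumed) uses it independently. P = 1 − (1 − q)^n − nq(1 − q)^(n−1).

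- For the 35 + 75 = 110 expected contact cases: 65% at q = 2%, 98% at q = 5%, above 99.9% at q = 10%.
- For the 35 household cases alone, if the term household contacts is read literally: 15%, 53% and 88%.
- For all 250 + 35 + 75 = 360 cases there are 360 × 359/2 = 64,620 pairs. Expected sharing pairs are 64,620 × q²: about 26 at 2%, 162 at 5% and 2,585 at 20%.

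So some sharing is likely without any transmission at the venue, even where it is rare per pair.

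**4. What a linked-versus-unlinked comparison could detect.** Same-household pairs are left out because they already share a home. The protocol puts the Index/neighbourhood percentage between 10% and 60%, so 75 neighbourhood cases give 7.5 to 45 linked pairs. Its 30% power scenario gives 22.5, taken as 22. With four unlinked pairs per linked pair, pairs treated as independent, and assumed sharing rates:

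| Sharing, linked vs unlinked | 22 linked pairs | 43 linked pairs |
|---|---|---|
| 30% vs 10% | 64% | 87% |
| 20% vs 5% | 60% | 83% |
| 20% vs 10% | 29% | 45% |

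The 43 column is the count with household pairs included (21 + 22). It is also close to the top of the neighbourhood range. Linked Index/Index pairs would add some: at most 10% of 250 = 25 Index cases, or about 12 pairs if they cluster in twos. Against that, strict matching of each neighbourhood case to its own Index case leaves 52.5 unlinked to 22.5 linked, about 2.3 to 1 rather than 4 to 1. Dependence between pairs and several venue types reduce power further.

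**The case against.** The strongest objection is that a journal article condenses the full protocol, and network methods are commonly left to that or to the analysis plan. The Discussion signals joint use of genomic and network data, and nothing excludes a linked-versus-unlinked comparison. This stands in part: the limitation lies in the stated analysis, not in the data. But the article does state a venue analysis, and that analysis cannot carry the use considered for it.

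Three stronger readings are tempting and are not supported.

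- A reader might infer that the study cannot meet its objective on epidemiological relatedness. The household, neighbourhood and travel-time comparisons largely serve that objective and are unaffected.
- A reader might infer a commitment to act on the busiest venues. No rule for flagging venues is given, and the hotspot sentence is conditional twice over.
- A reader might infer that a quarter to three quarters of unrelated pairs share a venue. That range (25% to 76%) needs assumed use of 30% to 50%; at 2% to 20% use the figure is 0.1% to 18.5%.

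It is also fair to say that household contacts may be loose wording for all contacts with TB, since the sample-size section counts neighbourhood cases. That is an ambiguity to settle.

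**Conclusion.** The point holds in a limited form. The venue analysis as stated has no comparator, and bare sharing cannot separate a popular venue from a place of transmission. How often unrelated cases share is unknown: from under 1% to about 76% of pairs over assumed venue use of 2% to 50% and 3 to 5 venues, with independent use. That uncertainty is itself the reason a comparator is needed.

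Genomically unlinked pairs provide one, because genetic distances and travel times are already planned. The comparison shows whether sharing goes with genomic linkage; it does not give risk relative to people without TB. With about 22 linked Index/neighbourhood pairs under the 30% scenario, power is 29% to 64% for the contrasts examined. It would therefore be wrong to make significance a condition for calling a venue a possible hotspot, and a result by venue type cannot identify a particular location. Only a secondary inference is affected.

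**What to change.** In *2) Whole-genome sequencing and social network analysis*, replace the sentence on shared meeting places with a comparison:

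- Use case pairs from different households, and say explicitly that Index and neighbourhood cases are included.
- Compare the odds of sharing a venue between genomically linked and unlinked pairs, at the SNP levels already defined.
- Stratify or adjust for neighbourhood and travel-time band.
- Base inference on permutation or case-level resampling, because each case appears in many pairs.
- Report the result as exploratory, with confidence intervals. Make no hotspot statement from sharing alone, and do not read a non-significant result as ruling a venue out.

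The cost is modest extra analysis, and precision will be limited. No new group needs to be interviewed, but the questionnaire must record venues specifically enough to match them between cases. The article does not show whether it does, so this should be checked before interviews begin.

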### Sample size

#### Prevalence in neighbourhoods

The community estimate of TB prevalence from the Indonesian National Prevalence Survey result for Java was 0.5% (95% CI 0.4 to 0.6%) [22]. We expect a higher rate among TB neighbourhoods, and pragmatically (to justify a policy change), a prevalence of approximately 1.25% culture positive TB cases will be needed in the neighbourhoods. With 4500 neighbourhood participants, the 95% confidence interval around 1.25% will be 0.9 to 1.6%, comfortably above the community estimate.

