#### 1) Prospective cohort study

*Study participation and recruitment*. From 250 bacteriologically-proven TB patients (Index case) living within one of the six selected CHC areas of Bandung City (as described above), we will conduct active case finding among household contacts (approximately four people per household) and neighbourhood members. Trained research staff will interview all persons aged 10 years and above living in the same household as the Index case, as well as all those living in the five houses closest to the Index case. We will record all subjects in the target households and assess their eligibility. We will not exclude any person with extra-pulmonary TB or being re-treated for TB for screening or follow-up. We will exclude any person in a household who normally lives at another location, or children under the age of 10 years.

The TB nurse in each recruitment site (CHC or hospital) will identify potential Index cases, ensure they are resident in the selected area and seek consent for their contact details to be forwarded for the study. Research staff will then contact consenting Index cases to arrange a time to visit them and their household when most household members are likely to be present. At the visit, further information will be provided and written informed consent obtained. The Index case will also be informed that we wish to contact neighbourhood households and their consent sought before proceeding. Research staff will identify five houses that are the closest in proximity from the Index case house. Within each identified neighbourhood household, the same procedure of informed consent will be followed. The research staff will be instructed not to reveal the identity of the Index case. Consent for any household members aged between 10 and 18 years will be sought from their parent or guardian.

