### Outcome measures and statistical analysis

We will categorize TB for Index and household/neighbourhood contacts into four categories: definite TB, probable TB, possible TB, and not TB. Subjects are categorised as definite TB if their *Mtb* culture or Xpert MTB/RIF positive; probable TB if they have TB symptoms, chest x-ray suggestive of TB, and AFB smear-positive but culture negative/not done; possible TB if they have TB symptoms and/or chest x-ray suggestive of TB but all bacteriology examinations negative/not done; and not TB if there was no evidence of TB on a symptom review or investigations. Chest x-rays will be classified as normal, suggestive active TB, suggestive inactive TB, or abnormal not TB based on the radiology report.

The key outcomes of this study are to estimate the TB prevalence and incidence in neighbourhoods around known TB cases, compared to households of known TB cases. TB prevalence defined as the number, percent and 95% confidence intervals (CI) of positive TB cases, according to each TB definition (definite, probable, possible), will be estimated. These proportions will be compared between households, neighbourhoods, and estimates from the Indonesian National Prevalence Survey for Java/Bali. TB incidence defined as incidence rates and 95% CI of positive TB cases according to each TB definition (definite, probable, possible), will be calculated per 1000 person-days. Person-days will be calculated as the days from the date of baseline examination to either: a) the date of TB diagnosis, b) date of death (if died) as reported by household member, c) date of 12-month follow-up examination, or d) date left the neighbourhood area for any household member who has left the area before the 12-month follow-up.

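### The planned 95% CI of 0.9 to 1.6% for neighbourhood prevalence carries no design effect, although the 4500 neighbours are sampled as 250 clusters of five nearby houses

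*Protocol article*

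**What the plan says.** **Precision target** (Protocol article, Prevalence in neighbourhoods). The community prevalence for Java is put at 0.5%, with a 95% CI of 0.4 to 0.6%. To justify a policy change, "a prevalence of approximately 1.25% culture positive TB cases will be needed in the neighbourhoods". The precision claim follows: "With 4500 neighbourhood participants, the 95% confidence interval around 1.25% will be 0.9 to 1.6%, comfortably above the community estimate". The section mentions no cluster size, ICC or design effect.

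**Sampling** (Protocol article, 1) Prospective cohort study). Recruitment is built on Index cases: "From 250 bacteriologically-proven TB patients (Index case) living within one of the six selected CHC areas of Bandung City". Around each one, staff interview household members aged 10 or over, "as well as all those living in the five houses closest to the Index case".

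**Analysis** (Protocol article, Outcome measures and statistical analysis). The relevant sentence is "TB prevalence defined as the number, percent and 95% confidence intervals (CI) of positive TB cases, according to each TB definition". Incidence rates also get 95% CIs, and proportions are compared between households, neighbourhoods and the national survey. No method is named for any interval or comparison.

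**The concern.** A confidence interval computed from the number of people assumes that each person contributes independent information. Here the sampling unit is the neighbourhood of an Index case, and within it the house. People in five houses next to one another share exposure, housing and socio-economic conditions.

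The article itself gives reasons to expect some correlation. The Introduction refers to shared socio-economic risk factors. The genomic section expects matching between Index and neighbourhood cases to lie above the community level. The Discussion allows for transmission hotspots.

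If such correlation exists, 4500 neighbours carry less information than 4500 independent people, and the interval quoted to justify the sample size is narrower than the design will deliver. The stake is how honestly the precision is stated for a prevalence that is meant to inform policy.

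**Working it through.** **Inputs.** From the sample-size section: n = 4500, p = 0.0125 (about 56 cases) and a community upper limit of 0.6%. From the cohort section: 250 Index cases and five houses each. Derived: 1250 houses, m = 4500/250 = 18 people per neighbourhood, and 4500/1250 = 3.6 per house. The ICC is not in the documents and is assumed over a range.

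**Step 1: reproduce the plan's figure.**
- SE = √(0.0125 × 0.9875 / 4500) = 0.166 percentage points.
- 1.25 ± 1.96 × 0.166 gives 0.925 to 1.575%, printed as 0.9 to 1.6%.
- The exact (Clopper-Pearson) interval, 0.946 to 1.619%, also prints as 0.9 to 1.6%. The Wilson interval, 0.964 to 1.619%, prints as 1.0 to 1.6%.

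The stated interval is therefore the one for a simple random sample. The other interval in the sample-size text, 6.3 to 13.7% around 10% of 250, is also plain Wald: 1.96 × √(0.1 × 0.9 / 250) = 3.72 points.

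**Step 2: add a design effect.** DEFF = 1 + (m − 1) × ICC = 1 + 17 × ICC. The effective n is 4500/DEFF, and the half-width of 0.325 points is multiplied by √DEFF.

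| Assumed ICC | DEFF | Effective n | 95% CI | Widening |
|---|---|---|---|---|
| 0 | 1.00 | 4500 | 0.93 to 1.57% | none |
| 0.01 | 1.17 | 3846 | 0.90 to 1.60% | 8% |
| 0.02 | 1.34 | 3358 | 0.87 to 1.63% | 16% |
| 0.05 | 1.85 | 2432 | 0.81 to 1.69% | 36% |

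**Step 3: is this ICC range reasonable?** If prevalence varies between neighbourhoods with coefficient of variation k, then ICC = k² × p/(1 − p). With k = 1 this is 0.013, and with k = 2 it is 0.051. The table thus covers roughly k = 1 to 2, which is itself an assumption.

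**Step 4: where would the statements in the plan change?**
- The printed 0.9 to 1.6% changes when the lower limit falls below 0.85%: DEFF = (0.40/0.3246)² = 1.52, so ICC = 0.52/17, about 0.03 (k about 1.55).
- The lower limit reaches 0.6% at DEFF = (0.65/0.3246)² = 4.0, so ICC = 3.0/17, about 0.18.

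**Step 5: unequal cluster sizes.** With an assumed coefficient of variation of 0.5 in cluster size, DEFF = 1 + (18 × 1.25 − 1) × ICC. At ICC 0.05 this is 2.075, and the interval is 0.78 to 1.72%.

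**The case against.** **The printed figure may still be right.** At ICC 0.01 or 0.02 the recalculated interval rounds to the same 0.9 to 1.6%. If the correlation is confined to single houses, DEFF = 1 + 2.6 × ICC, and even an ICC of 0.20 gives only 1.52. This stands: the documents do not show that the one-decimal figure is wrong, only that nothing in it allows for clustering.

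**A raised average is not clustering.** Every sampled neighbourhood contains an Index case. A uniform rise in risk lifts the mean without creating correlation, and the Discussion leaves open that reactivation predominates. This also stands in part. The size of the ICC cannot be derived from the documents. That it is exactly zero is nevertheless hard to reconcile with shared risk factors and local transmission.

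**The main comparison is safe.** The interval is used to argue that neighbourhoods lie above the community estimate, and that holds over the whole table. A reader might infer that the sample is too small for its purpose. The documents do not support that.

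**The analysis may already handle it.** A reader might also infer that the final intervals will under-cover, or that the household-neighbourhood comparison will have the wrong standard error because both groups share an Index case and locality. The analysis section neither assumes independence nor rules out cluster-robust methods, and a condensed article may leave that choice to an analysis plan that is not shown. Those are risks to close off, not errors that have been shown.

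**Conclusion.** The point holds for the sample-size statement. It gives simple-random-sample precision for a cluster sample, and the direction of the error is clear: any positive correlation within a neighbourhood makes the true interval wider. For an assumed ICC of 0.01 to 0.05 and equal clusters of 18, the widening is about 8 to 36%.

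The consequence is limited. The number of participants remains adequate for the stated purpose, and the separation from the community estimate withstands far more clustering than the assumed range. This is a worthwhile correction to an optimistic precision figure, not a threat to the design. The size rests wholly on the assumed ICC.

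**What to change.** 1. In the sample-size section, state an assumed ICC or design effect for neighbourhoods of about 18 people, and give the resulting interval. For example, it is about 0.8 to 1.7% at ICC 0.05. Add that the lower limit still exceeds the community upper limit of 0.6%.
2. In the analysis section, state that the CIs for prevalence and incidence, and the household-neighbourhood comparison, treat the Index-case cluster (the index household plus its five neighbouring houses) as the sampling unit. Suitable methods are GEE or survey linearisation for prevalence and cluster-robust Poisson regression for incidence. If the full analysis plan already says so, a reference to it is enough.

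The cost is about two sentences and a slightly less favourable stated interval. Enrolment, visits and data collection do not change.
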